## Abstract

**Objective:** The aim of this paper is to describe the protocol of pilot cluster randomized controlled trial (RCT) that will evaluate the effects of a lifestyle-based intervention. The *Archena Infancia Saludable* project will have several objectives. The primary objective of this project is to determine the 6-month effects of a lifestyle-based intervention on adherence to 24-h movement behaviors and Mediterranean diet (MedDiet) in schoolchildren. The secondary objective of this project is to test the intervention effects of this lifestyle-based intervention on a relevant set of health-related outcomes (i.e., anthropometric measurements, blood pressure, perceived physical fitness, sleep habits, and academic performance). The tertiary objective is to investigate this intervention’s “halo” effect on parents’/guardians’ 24-h movement behaviors and adherence to the MedDiet. **Methods:** The *Archena Infancia Saludable* trial will be a cluster RCT submitted to the Clinical Trials Registry. The protocol will be developed according to SPIRIT guidelines for RCTs and CONSORT statement extension for cluster RCTs. A total of 153 eligible parents/guardians with schoolchildren aged 6–13 years will be randomized into an intervention group or a control group. This project focuses on two fundamental pillars: 24-h movement behaviors and MedDiet. It will mainly focus on the relationship between parents/guardians and their children. Behavior change strategies for dietary and 24-h movement behaviors in schoolchildren will be based on healthy lifestyle education for parents/guardians through infographics, video recipes, brief video clips, and videos. **Conclusions:** Most of the current knowledge on 24-h movement behaviors and adherence to the MedDiet is based on cross-sectional or longitudinal cohort studies, warranting a need to design and conduct RCTs to obtain more robust evidence on the effect of a healthy lifestyle program to increase 24-h movement behaviors and to improve adherence to the MedDiet in schoolchildren.

## 1. Introduction

The 24-h movement guidelines for youth have shifted the focus from individual physical activity (PA) components to an integration of all movement-related behaviors in the 24-h time-use continuum [1]. These guidelines indicate that children and adolescents (aged 5–17 years) should engage daily in at least 60 min of moderate-to-vigorous PA, restrict their recreational screen time (≤120 min per day for children/adolescents), and obtain adequate sleep duration (e.g., 9–11 h per day for children, 8–10 h for adolescents) in a period of 24 h [1,2]. Thus, clustering and interactions between all 24-h movement guidelines should be promoted to improve health outcomes [3]. PA, sleep duration, and sedentary behavior (including screen time) have been related to a wide range of essential health and developmental outcomes in a young population [4]. To date, most studies have investigated these movement behaviors in isolation. However, recently, attention has turned toward a comprehensive method that acknowledges the interdependence and interconnectedness of 24-h movement behaviors [3,5]. Such guidelines note that the clustering and interactions among all domains of 24-h movement behaviors need to be addressed to enhance health results (e.g., lower risk of obesity, type 2 diabetes, depression and suicidal ideation, higher physical fitness) [3,6,7,8,9]. Despite these attributed health benefits, a recent meta-analysis reported a global rate of adherence to the 24-h movement guidelines of only 7.12% [10].

Concerning eating habits, the World Health Organization (WHO) advises a healthy diet to help protect against malnutrition as well as noncommunicable diseases such as cancer, cardiovascular diseases, stroke, and type 2 diabetes [11]. However, the need to improve dietary quality on a global scale has recently been highlighted [12]. In this sense, the Mediterranean Diet (MedDiet) is a dietary pattern well known worldwide for its distinctive characteristics and health benefits [13,14,15]. The MedDiet includes an eating pattern rich in fruits and vegetables (seasonal), legumes, nuts, whole grains, and olive oil as the main dietary fat with a greater intake of white or lean meats rather than red or processed meats, moderate consumption of dairy products (cheese, milk), moderate consumption of fish, eggs, and small intakes of wine with meals (only in adults) [16,17]. Supporting this notion, scientific evidence has demonstrated the inverse relationship between the MedDiet and noncommunicable diseases in adults (e.g., cancer, metabolic syndrome, hypertension, and cardiovascular diseases) [18]. Specifically, among young people, greater adherence to the MedDiet has been associated with greater anti-inflammatory potential [19]. Unfortunately, even though it is a healthy dietary pattern supported by evidence, a systematic review has pointed out the clear trend of decreasing adherence to the MedDiet in Mediterranean countries, especially among children [20,21]. For instance, Cabrera et al. [20] reported an overall rate of only 10% with high adherence to the MedDiet among a young population. As possible reasons for this trend, westernization of diets [22], urbanization [23], lifestyle changes [24,25], economic factors [26], and lack of knowledge and education [27] (among others) have been proposed.

Previous studies have found an association between meeting the 24-h movement guidelines and healthier dietary patterns [28,29]. Regarding MedDiet, only one previous cross-sectional study (in adolescents) has found that meeting all three 24-h movement guidelines has been related to greater adherence to the MedDiet compared to those who did not meet these guidelines [30]. It is possible that the low prevalence of 24-h movement guidelines reported worldwide [10] and in Spain [28] may be another factor to be taken into account in the low adherence to the MedDiet currently described [20,21]. Although the need for interventions focusing on improving adherence to the 24-h movement guidelines [10] and MedDiet [25] has been previously suggested, the literature on this matter is limited. More specifically, to our knowledge, no previous randomized controlled trial (RCT) has verified the effect of a healthy lifestyle program on both adherence to 24-h movement behaviors and the MedDiet in schoolchildren. In addition, although associations between 24-h movement behaviors or adherence to the MedDiet and numerous health-related outcomes (e.g., blood pressure, obesity-related indicators, physical fitness, sleep quality) have been previously reported, there is a lack of scientific evidence on the effect of healthy lifestyle interventions, including their interaction effects on particular health-related outcomes in addition to academic performance, when both are implemented at the same time. This also denotes the need for well-designed RCTs focused on this matter.

The objective of this paper is to describe the protocol of a pilot cluster RCT that will evaluate the effects of a lifestyle-based intervention. The *Archena Infancia Saludable* project will have several objectives. The primary objective of this project is to determine the 6-month effects of a lifestyle-based intervention on 24-h movement behaviors and adherence to the MedDiet in schoolchildren. Furthermore, the secondary objective of this project is to test the intervention effects of this lifestyle-based intervention on a relevant set of health-related outcomes (i.e., anthropometric indicators, resting blood pressure and heart rate, sleep problems, health-related quality of life, perceived physical fitness, and academic performance). Likewise, the tertiary objective of this study is to verify this intervention’s “halo” effect on 24-h movement behaviors and adherence to the MedDiet. We hypothesize that the *Archena Infancia Saludable* project will achieve improvements with small-to-medium effects on 24-h movement behaviors and adherence to the MedDiet in schoolchildren.

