### 2.5. Statistical Procedures

#### 2.5.1. Sample Size

The sample size calculation was performed following the indications by Donner et al. [43]. First, we calculated the sample sizes without adjustment for clustering (*N_0_*). For this purpose, the statistical analysis in this study involved several parameters, including the threshold probability for rejecting the null hypothesis (α), which represents the type I error rate, and the probability of failing to reject the null hypothesis under the alternative hypothesis (*β*), representing the type II error rate. In addition, the proportion of subjects in the intervention group (*q*_1_) and control group (*q*_0_), the effect size (Cohen’s *d*), and the standard deviation of the outcome in the population (*σ*) were calculated. Thus, an *α* value (two-tailed) of 0.05 and a *β* value of 0.20 were established so that the standard normal deviation for *α* is *Z_α_* = 1.960 and for *β* is *Z_β_* = 0.842. The proportion of subjects in both the intervention and control groups will be similar (*q*_1_ = 0.50; *q*_0_ = 0.50). Our study will be powered to detect medium-sized effects (i.e., Cohen’s *d* = 0.5), and the standard deviation of the outcome in the population will be 1.0.
$$N_{0}=\frac{\left(\frac{1}{q_{1}}+\frac{1}{q_{0}}\right)\;*\;(\left(Z_{\alpha \;}+Z_{\beta }{)}^{2}\right)}{{\left(\frac{d}{\sigma }\right)}^{2}}$$
$$N_{0}=\frac{\left(\frac{1}{0.50}+\frac{1}{0.50}\right)*(\left(1.960+0.842{)}^{2}\right)}{{\left(\frac{0.5}{1.0}\right)}^{2}}$$
*N*_0_ = 125.58 ≈ 126 participants

Second, we calculated the sample size with adjustment for clustering (*N*_1_). For previous studies in this specific population, we assumed an average household size (*m*) of 1.2 participants according to previous studies performed in the same region [44,45]. Moreover, the within-cluster correlation coefficient (*ρ*) was established as 0.5.
Design effect = 1 + (*ρ* × (*m* − 1))
Design effect = 1 + (0.5 × (1.2 − 1)) = 1.1
*N*_1_ = *N*_0_ × Design effect => 138.14 ∗ 1.1 = 138.142 ≈ 138 participants

Third, we further assumed a 10% drop-out rate, which was estimated using the following formula:*N*_3_ = *N*_2_ / (1 − % losses)
*N*_3_ = 138/(1 − 0.1) = 153 participants

Thus, a minimum sample size of 153 participants for the whole sample will be required to perform this study.

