#### 2.5.2. Statistical Analysis

The mean (*M*) and standard deviation (*SD*) will be provided for quantitative variables, while frequencies (*n*) and percentages (%) will be given for qualitative variables. Kolmogorov-Smirnov’s test with Lilliefors correction and Levene’s test will be used to assess the normality of data and the equality of variances, respectively. Thereafter, Student’s *t* test or Mann–Whitney’s *U* test for two-group comparisons will be used in relation to meeting the normality assumption. Pearson’s chi-square (χ^2^) test will be employed to verify associations between qualitative variables. For quantitative variables, the relationship will be tested through Spearman’s rho (*ρ*) or Pearson’s *r*, based on the normality assumption. Preliminary analyses will be conducted to identify the frequency, range, variability, and distribution pattern of each variable to apply the most appropriate statistical test when comparisons are needed. Since this RCT has an experimental design with two data collections of the primary, secondary, and tertiary outcomes, the first at baseline (*t*_0_ = 0 weeks) and the second after intervention (*t*_1_ = 24 weeks) in both the intervention and control groups, we will apply a comparative analysis between these measures to establish differences between groups. To evaluate the intervention effect, multilevel mixed-effects regression models with repeated measures will be conducted for each dependent variable. Then, multivariate analyses will be performed, considering the autocorrelation between repeated measures. Both intention-to-treat (ITT) (which measures the effect of assigning an intervention) and per-protocol (PP) analysis (which measures the effect of receiving an intervention) approaches will be applied for the data analysis. All statistical analyses will be conducted using Stata software (Stata, College Station, TX, USA) (version 17.0) for Windows. A *p* value ≤ 0.05 will determine statistical significance.

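### The repeated-measures model leaves open how baseline enters; fixing a baseline-adjusted estimator would gain precision at no cost

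*Protocol article*

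**What the plan says.** The relevant statements are in three sections of the protocol article.

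- **Section 2.5.2 (Statistical Analysis).** Outcomes are measured at baseline and at 24 weeks in both arms. For the effect, "To evaluate the intervention effect, multilevel mixed-effects regression models with repeated measures will be conducted for each dependent variable". Multivariate analyses that allow for autocorrelation between the two measures follow. The section does not say whether the effect is a group-by-time term, whether the arms share one baseline mean, or whether baseline is a covariate.
- **Section 2.5.1 (Sample Size).** "Our study will be powered to detect medium-sized effects", set at d = 0.5, and "the standard deviation of the outcome in the population will be 1.0". The two-sample formula has no term for the correlation between baseline and follow-up.
- **Section 1 (Introduction).** The hypothesis is that the project "will achieve improvements with small-to-medium effects on 24-h movement behaviors and adherence to the MedDiet in schoolchildren".

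Section 2.6.4 lists age and sex among the covariates, and section 2.6 says that the outcomes are measured both at enrolment and after the programme.

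**The concern.** A mixed model with baseline and week 24 both in the outcome vector can be fitted in more than one way, and the ways differ in precision. A common form has group, time and group-by-time terms with a free baseline mean in each arm. With two visits, its interaction term is the difference between arms in mean change. That estimator carries the noise of the baseline measurement in full. An analysis that adjusts for baseline, or that gives both arms one baseline mean, uses the baseline only as far as it predicts follow-up, and it is more precise at any r below 1.

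Two things are at stake. The sample-size formula matches neither form, so the power actually achieved depends on a choice that the article leaves open. Also, precision that the collected data could provide may be lost in a trial of only 153 participants.

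**Working it through.** **Inputs from section 2.5.1.** Two-sided alpha 0.05 (Z = 1.960), beta 0.20 (Z = 0.842), equal allocation, d = 0.5, SD 1.0, mean household size 1.2, within-cluster correlation 0.5, dropout 10%.

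**The plan's own figure.**
- N0 = (1/0.50 + 1/0.50) × (1.960 + 0.842)² / 0.5² = 4 × 7.851 / 0.25 = 125.6, against 125.58 and then 126 in the article.
- Design effect = 1 + 0.5 × (1.2 − 1) = 1.1, and 125.6 × 1.1 = 138.2, against 138.
- 138 / 0.9 = 153.3, against 153.

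The figure reproduces. The printed line 138.14 × 1.1 = 138.142 must mean 125.58 × 1.1; this slip does not affect the result.

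**Effective sample after dropout and clustering.** 138 / 1.1 = 125.5.

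**Variance factor v for each estimator,** in units of σ², with equal variance at both visits:
- Week 24 only, as in the article's formula: v = 1.
- Difference in change (unconstrained group-by-time): v = 1 + 1 − 2r = 2(1 − r).
- Baseline-adjusted (ANCOVA or, to a close approximation, a common baseline mean): v = 1 − r².
- Ratio of the last two: 2(1 − r) / [(1 − r)(1 + r)] = 2/(1 + r), which exceeds 1 for every r below 1.
- The change contrast is worse than week 24 only when 2(1 − r) > 1, that is, when r < 0.5.

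**Power** = Φ( d × √(125.5/v) / 2 − 1.96 ). For example, at d = 0.5 and r = 0.3:
- Change contrast: v = 1.4, 0.25 × √89.6 = 2.37, and 2.37 − 1.96 = 0.41, so power is 66%.
- Baseline-adjusted: v = 0.91, 0.25 × √137.9 = 2.94, and 2.94 − 1.96 = 0.98, so power is 84%.

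The documents give no r, so a range is shown for d = 0.5:

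| r (assumed) | Power, change contrast | Power, baseline-adjusted | Variance ratio 2/(1+r) | Detectable d at 80%, change / adjusted |
|---|---|---|---|---|
| 0.3 | 66% | 84% | 1.54 | 0.59 / 0.48 |
| 0.4 | 72% | 86% | 1.43 | 0.55 / 0.46 |
| 0.5 | 80% | 90% | 1.33 | 0.50 / 0.43 |
| 0.6 | 88% | 94% | 1.25 | 0.45 / 0.40 |

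**Side check on smaller effects,** with the article's own formula (v = 1): power is 80% at d = 0.5, 61% at 0.4, 50% at 0.35 and 39% at 0.3. At d = 0.2 it is 20%. The article puts no number on a small effect, so 0.2 is an assumption.

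**The case against.** The strongest objection is that section 2.5.2 does not describe the less precise model. It names a family of models, and a repeated-measures mixed model with a common baseline mean belongs to that family. How baseline is parameterised is also a detail that an article may leave to an analysis plan. This stands. A reader might infer that the model gives up baseline adjustment, but the text neither states nor excludes that.

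It is also fair that the change contrast is not always a loss against the stated power. It reaches 80% at r = 0.5, 88% at r = 0.6 and 95% at r = 0.7. A shortfall below 80% therefore needs both an unconstrained model and a correlation under 0.5. What remains is the comparison with baseline adjustment, which the change contrast loses at every r below 1.

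A reader might also infer from the hypothesis of small-to-medium effects that the trial is underpowered for its own aim and would most likely miss a hypothesised effect. The documents do not support that. Section 2.5.1 openly claims 80% power for d = 0.5 only, and the design delivers it. Power is at least 50% from d = 0.35 upwards even under the week-24-only formula, which is not the planned model. Nor does anything say that a non-significant result would end the programme. The Discussion calls this a single-school pilot meant to improve the intervention through feedback, and it sets no stop-or-go rule.

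**Conclusion.** The point holds in conditional form. The article leaves open how baseline enters the effect model. If the model is fitted with an unconstrained group-by-time term, its variance is 1.25 to 1.54 times that of a baseline-adjusted analysis for r from 0.6 down to 0.3. Power at d = 0.5 is then lower by about 6 to 18 percentage points (88% against 94% at r = 0.6; 66% against 84% at r = 0.3). Below r = 0.5 it also falls short of the planned 80%.

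This rests on an assumed range for r, equal variance at both visits, a quantitative outcome, and the article's design effect of 1.1 and 10% dropout applied to both estimators. It is a free improvement, not a demonstrated error.

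As a side note, the hypothesis reaches below the effect for which the trial is powered. Baseline adjustment does not fully close that gap: at d = 0.2 it gives only about 35% power even at r = 0.7. A non-significant result should therefore be read through its confidence interval.

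**What to change.** 1. Add one sentence to section 2.5.2: the intervention effect on each quantitative outcome with a baseline value is the week-24 difference between arms, adjusted for that baseline value. Estimate it in one of two ways:
   - ANCOVA with a household random intercept; or
   - the repeated-measures mixed model with one common baseline mean for both arms, a household random intercept and within-child correlation.
2. Name age and sex, already listed in section 2.6.4, as covariates in that model.
3. Add a sentence to section 2.5.1 saying that the 80% power refers to d = 0.5 under the stated formula, with the power at d = 0.35 (about 50%) and at a stated small effect. Say that non-significant results will be interpreted through confidence intervals.

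The cost is a few sentences. There is no new data collection and no change to the sample size. The common baseline mean relies on baseline being measured before allocation, as section 2.2.4 intends.

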## 2. Materials and Methods

### 2.1. Design

The *Archena Infancia Saludable* (Figure 1) project will be a cluster randomized, parallel-group, clinical trial. The protocol was developed according to SPIRIT guidelines for RCTs [31] and CONSORT statement extension for cluster RCTs [32].

### 2.2. Setting

#### 2.2.1. Procedure

The unit of randomization, intervention, and cluster analysis are the participating parents/guardians with schoolchildren aged 6–13 years, who will be randomized into an intervention group or a control group. The study will be conducted at four different times during one academic year:(a)*First phase.* For four months, we will prepare protocols, set up measurement techniques, enroll the study participants, and collect the baseline data from both parents/guardians and their children.(b)*Second phase*. The intervention program will be conducted for six months.(c)*Third phase*. For one month, we will collect postintervention data from both parents/guardians and their children.(d)*Fourth phase*. In the last month, the control group will receive all the contents of the healthy lifestyle program upon completion of the program by the intervention group.

#### 2.2.2. Rationale for the Age Group Chosen

This project will target schoolchildren aged 6–13 years. This age group was chosen because childhood is a critical period for adopting daily routines and habits. In addition, the *Archena Infancia Saludable* program will be focused on parents/guardians because they are in a key position to encourage healthy behaviors among their children [33]. Furthermore, an additional reason that justifies this choice of study population lies in the low adherence to the MedDiet [20,21,25] and meeting all the 24-h movement guidelines [4,10] reported in schoolchildren.

#### 2.2.3. Schoolchildren Eligibility

Regarding the inclusion criteria, schoolchildren aged 6−13 years will be eligible. The exclusion criteria will be defined as follows: (a) participants with any pathology that contraindicates exercise or that requests special attention; (b) participants under pharmacological treatment that prevents them from receiving the contents of the activities of the program; (c) participants or parents/guardians presenting Spanish learning difficulties in understanding the contents of the questionnaires; (d) participants whose parents/guardians do not authorize participation in the research project; or (e) participants who decline to participate in the research project.

#### 2.2.4. Recruitment and Randomization

In this pilot study, recruitment will be performed in one school randomly selected from Archena (Region of Murcia, Spain). Previously, we will contact the directors of all schools of Archena (Region of Murcia, Spain), and we will release announcements through local media channels. Any parent/guardian with a child who meets the inclusion criteria indicated above will be invited to participate. A blinded randomization of the participants into the intervention or control group will be performed using the list of encrypted codes of the participants using the software SPSS (IBM Corp, Armonk, NY, USA) (version 25.0) for Windows. To decrease the risk of selection bias during the assessments, a researcher who will not participate in either the data collection or in the statistical analysis will be responsible for randomizing the groups after the intervention. This process will be conducted immediately after the collection of baseline data. The researchers who will participate in the data collection will not know to which group the schoolchildren belong, neither at the baseline nor at the postintervention measurements.

### 2.3. Intervention

The intervention group will complete the *Archena Infancia Saludable* interdisciplinary program for six months. The interdisciplinary research team comprised nutritionists, physicians, PA and sports science professionals, physical education teachers, nurses, and psychologists. The investigators responsible for carrying out the intervention program will not participate in data collection or statistical analysis, so they will not be aware of the participants’ group assignment.

The *Archena Infancia Saludable* project will focus on two fundamental pillars: 24-h movement behaviors and MedDiet. Some examples of the contents of the intervention program are shown in Figure 2. The project will mainly focus on the relationship between parents/guardians and their children. Furthermore, the program includes a behavioral approach (i.e., nutritional education), which encourages the responsibility among all the participants to maintain healthy behavioral changes over the long term [19,34].

The nutritional approach will follow the MedDiet model [13]. We will not impose any caloric restriction since we aim to establish a healthy diet based on the MedDiet [14,25]. Concerning the 24-h movement behaviors, parents/guardians will be told to encourage their children to adopt an active lifestyle with a daily equilibrium of PA, sedentary behavior, and sleep that will support their healthy development [1]. Dietary and 24-h movement behavior changes in schoolchildren will be based on healthy lifestyle education for parents/guardians by infographics, video recipes, information pills, and videos. The contents of these materials have been created by the research team following international and national guidelines for PA [1,35,36], sedentary behavior [1], sleep duration [1,37], MedDiet [38], and healthy eating guidelines [39,40].

The intervention will be performed by the communication application for schools TokApp (TokApp Online S.L., Vigo, Spain). All the contents of the intervention programs will be delivered online. In line with our hypothesis, only parents/guardians will receive the contents of the intervention. We will try to verify whether intervening in parents/guardians has an impact on 24-h movement behaviors and adherence to the MedDiet in their children. Thus, parents/guardians will receive three different contents weekly (i.e., infographics, video recipes, information pills, or videos) related to 24-h movement behaviors (i.e., PA, sedentary behavior, sleep duration) or MedDiet. In addition, each launched content will be available until the end of the intervention for those who have not been able to view it at the time of its launch. To not discriminate participants from the control group, all project materials will be offered to parents/guardians allocated to the control group at the end of the intervention phase as well. The researchers responsible for sending the contents of the intervention program through the communication application TokApp will not participate in data collection or statistical analysis after the intervention.

The length of the intervention (24 weeks during a school-academic year) falls within the time range used in the prior RCTs conducted on this topic (i.e., 20 weeks [41] and 60 weeks [42]). It has been previously described that when an intervention program is delivered, it can have a compensatory effect, so that participants discontinue other physical activities that they would normally have done otherwise. To address this issue, we will assess PA using activity monitors (i.e., accelerometers) for seven days at two different times during the study: at baseline and postintervention. Finally, any adverse effects will be documented and reported with trial outcomes.

